### Data Management

To ensure data privacy, research data will be identified using pseudonyms and will be stored on 2 password-protected servers only accessible by approved study staff members. Personal data (ie, username, phone number, and email address) will be stored separately from research data. Personal data and the pseudonym codes will only be matched in a handwritten key code list to protect the confidentiality of data. Identifiable data (including the key code list) will be deleted 2 years after the end of the project. The research data will then be anonymized. The anonymized data set will be stored for 10 years and shared with other research teams upon request using a repository that will be chosen by the consortium (advised by the DSMB).

### Data Monitoring

An independent DSMB will provide additional oversight on data safety, ethical procedures, and best clinical practices. A thorough data safety concept was developed and piloted in phase 1. This safety protocol outlines how adverse events will be identified, registered, acknowledged, and handled.

### Measures

#### Primary Measures

To investigate the primary efficacy, we will use a revictimization score derived from 2 measures: the Juvenile Victimization Questionnaire [33] and the bullying screener [34]. We will assess the child and parent reports of each measure while using the parent report for the primary outcome. The Juvenile Victimization Questionnaire is a widely and internationally used self-report measure to assess victimization in children aged 8 to 17 years. It consists of 34 items in the child version and 37 items in the parent version spanning 5 domains, namely, crime, child maltreatment, peer and sibling victimization, sexual victimization, and witnessing crime, with follow-up questions that also assess the frequency and perpetrators of the victimization events. A total of 3 supplemental items on electronic victimization will be assessed. In our study, the participants (caregiver and child) will be asked whether the child was exposed to the respective event and, if yes, whether it happened during the last 3 months (primary outcome–assessment period). The participants will respond with yes (1) or no (0), leading up to a total score, with higher scores indicating greater victimization exposure. The bullying screener [34] is a 6-item screening tool that assesses bullying as victim and offender. After the respective definition of bullying type, the participants are asked how often these things happened to the child or how often they have done this to others in the last 3 months. The participants then respond on a 4-point scale from never to a lot (*at least once a week*).

#### Secondary Outcomes

Secondary outcomes include relationship-related risk-taking behaviors (questionnaire on risky situations in relationships; [name], unpublished data, April 2021). The questionnaire comprises 14 risky situations (eg, “How often has someone done something to your child even though he or she did not want that and said ‘no’?”). Caregivers and children will be asked how often the risky situation occurred during the last 3 months (frequency). Afterward, they will rate how likely it is that the situation is followed by a positive and negative consequence (child’s risk appraisal) on a scale from 1 (very unlikely) to 5 (very likely). The structure (frequency and appraisal of risky situations) is based on the Cognitive Appraisal of Risky Events [67]. In addition, 6 case vignettes for risky situations are currently being developed to administer at postintervention assessment. Risky situations include being persuaded by a friend to swim far out to sea, witnessing bullying behavior in school, or a stranger standing very close to a child at a swimming pool. To assess functional relationship behavior across relationships with caregivers, siblings, and others, we will use 3 well-established measures: (1) the subscales communication and involvement of the Parenting Relationship Questionnaire [35], (2) the 7 subscales referring to “warmth and closeness” of the Sibling Relationship Questionnaires [36-38], and (3) the Relationship Problems Questionnaire [39]. Further details are provided in Multimedia Appendix 2.

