**Primary research**
**objectives**
To examine the efficacy of the selected candidate components on the primary outcome, the risk of revictimization, at follow-up (ie, 3 months after intervention; approximately 24 weeks after baseline)To examine the efficacy of the selected candidate components on the secondary outcomes (risk-taking behavior and functional behavior in relationships with the caregiver, siblings, peers, and others; Multimedia Appendix 2 [33-55] provides a full list of outcomes [[name], unpublished data, April 2021; [name], unpublished data, September 2021; [name], unpublished data, 2011; [name], unpublished data, April 2021; [name], unpublished data, August 2020; [name], unpublished data, March 2021]) at posttest assessment (ie, 1 week after intervention; approximately 12 weeks after baseline)

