#### Duration to Complete Each Module

During the program, parents will have 2 weeks to complete 1 module, with each module taking about 90 minutes to work through (including “homework” in the form of exercises with the child).

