#### Duration of the Intervention Package

Caregivers can work through the web-based program for a maximum of 10 weeks (conditions with the 3 candidate components *on* resulting in 6 weeks plus 4 weeks for the 2 basic modules). The duration of the intervention is reduced by up to 4 weeks if caregivers receive the basic modules only (experimental condition 1; Table 1).

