#### Content of Each Module

We have 6 intervention modules out of which only 4 will be put to test because modules 1 and 2 are already well investigated, with promising mental health benefits for the participants besides revictimization outcomes [20,21,64,65]. In addition to the 2 “basic modules,” a website area with literature recommendations and information texts on child maltreatment, self-injury, and suicidal behavior allows us to offer some level of support across all conditions, including the condition with the lowest component level across all intervention modules. The 6 intervention modules are described in detail in Textbox 3.

The 6 modules are embedded in a common website and independent of family assessment. The assessment is conducted via a professional tool for web-based surveys (refer to the *Data Collection for the Primary and Secondary Outcomes* section). The web-based intervention includes various multimedia features (texts, slides, videos, fictional audio recordings, and interactive tasks) to make the program easily accessible and attractive.

The intervention modules.

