**Module *Our feelings*—facilitating the emotional regulation of the child and the caregiver**
The second module provides basic knowledge about emotions and their functions. Caregivers are supported in recognizing and communicating their emotions as well as the child’s emotions. Parents are encouraged to attend to their child’s emotional needs, reflect on their emotions, and learn to keep them separate from their own emotional state, or at least recognize the difference and attempt to understand their child’s emotional reactions (eg, through storytelling and behavior attribution exercises). Emotional regulation strategies for the parent and the child are introduced and practiced.

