### Data Collection for the Primary and Secondary Outcomes

Each participant will be assessed on the web using *SoSci Survey* [66] 3 times, that is, at preintervention assessment (week 1), postintervention assessment (week 12), and 3-month follow-up assessment (week 24). Families will complete a brief questionnaire (5 minutes) on adverse events and child behavior during the past 2 weeks at the beginning of each module on the program website to ensure a closely monitored adverse event assessment. Multimedia Appendix 5 outlines the SPIRIT-recommended schedule of enrollment, interventions, and assessments. Families will receive a reimbursement of €30 (US $29.32 in the form of 2 vouchers: €20 (US $19.55) for caregivers and €10 (US $9.77) for the child) for their study participation after follow-up assessments.

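### The week-12 risk-situation frequency looks back 3 months, so much of its window precedes the content components and the posttest effect is diluted towards zero

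*Protocol article*

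**What the plan says.** The Secondary Outcomes section sets the recall period of the risk-situation questionnaire: "Caregivers and children will be asked how often the risky situation occurred during the last 3 months (frequency". It gives no shorter period for posttest.

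Textbox 1 places the test of the secondary outcomes, risk-taking behavior among them, under the primary research objectives, "at posttest assessment (ie, 1 week after intervention; approximately 12 weeks after baseline". The data collection section schedules assessments "at preintervention assessment (week 1), postintervention assessment (week 12), and 3-month follow-up assessment (week 24". The week-24 test of the same outcomes is listed as a secondary objective about enduring effects.

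On delivery, "parents will have 2 weeks to complete 1 module". "Caregivers can work through the web-based program for a maximum of 10 weeks", with the three content components "resulting in 6 weeks plus 4 weeks for the 2 basic modules". The basic modules go to every family and are not under test, because "modules 1 and 2 are already well investigated". They are numbered first and second ("The second module provides basic knowledge about emotions and their functions"), but no sentence makes that order a rule. The Study Design section says families are told that module sequence and timing depend on randomization.

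**The concern.** A posttest should describe behavior after the component has been received. Here the score is a count over the preceding 3 months, taken shortly after a program of at most 10 weeks. It therefore mixes time before the component with time after it. Families with a component on and families with it off should not differ in the earlier part, so the contrast shrinks towards zero.

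Risk-taking behavior is the behavioral step in the hypotheses for Watch Out! and for the identity component. A component that truly reduces it could look ineffective at the visit named in a primary research objective.

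The primary outcome avoids this problem: its 3-month recall is read at follow-up, 3 months after the intervention.

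**Working it through.** **Reproducing the plan's figure.** The Sample Size Calculations section gives N = 317 for d = 0.28, 80% power and alpha .10. With two equal groups, the noncentrality is d × √N / 2 = 0.28 × √317 / 2 = 2.49. A two-sided noncentral t test then gives power 0.8002 at N = 317 and 0.7991 at N = 316. The figure is reproduced.

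**Timeline.** Count weeks from program start. Basic modules take weeks 0 to 4, then each content module that is on takes 2 weeks in listed order. A component starts at week 4, 6 or 8, depending on how many content modules precede it. The order is inferred from the numbering.

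**Share of the window after the component starts.** Share = (posttest week − start week) / window length, with 3 months taken as 13 weeks.

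- Posttest 12 weeks after start: 8/13, 6/13 and 4/13 for the first, second and third slot. So 38%, 54% and 69% of the window comes before the component.
- Posttest 11 weeks after start: 7/13, 5/13 and 3/13. So 46%, 62% and 77% comes before.

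**Averaging to main effects.** Each main effect pools all conditions with the component on, so slots must be averaged. The four on/off patterns of the other two content components carry equal weight. For posttest at 12 weeks:

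- Watch Out! is always in the first slot: 8/13.
- You are safe here is first or second, half each: (8 + 6)/2 = 7, so 7/13.
- Who am I is first in one pattern, second in two and third in one: (8 + 6 + 6 + 4)/4 = 6, so 6/13.

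If posttest is 1 week after each condition's own end, it falls at week 7, 9 or 11 for one, two or three content modules. The averages become:

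- Watch Out!: (3 + 5 + 5 + 7)/4 = 5, so 5/13.
- You are safe here: (3 + 5 + 3 + 5)/4 = 4, so 4/13.
- Who am I: 3/13 in every pattern.

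**Diluted effect and power.** Diluted d = 0.28 × share, with N = 317, two-sided alpha .10 and unchanged SD. Cells show share; diluted d; power.

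| Posttest and window | Watch Out! | You are safe here | Who am I |
|---|---|---|---|
| 12 weeks after start, 13-week window | 8/13; 0.17; 46% | 7/13; 0.15; 38% | 6/13; 0.13; 31% |
| 11 weeks after start, 13-week window | 7/13; 0.15; 38% | 6/13; 0.13; 31% | 5/13; 0.11; 25% |
| 1 week after own end, 13-week window | 5/13; 0.11; 25% | 4/13; 0.09; 20% | 3/13; 0.06; 16% |
| 12 weeks after start, 12-week window | 8/12; 0.19; 51% | 7/12; 0.16; 42% | 6/12; 0.14; 35% |

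**Is it most of the window?** There are 12 combinations of a content component with an on/off pattern of the other two. With a 13-week window, more than half precedes the component's start in 5 of 12 on the week-12 schedule and in 11 of 12 if posttest follows each condition's own end. Counted to completion of the component, it is 12 of 12 either way.

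**Upper end of the expected effects.** At d = 0.46, undiluted power is 99%. It falls to about 81%, 71% and 59% with posttest 12 weeks after start, and to about 47%, 35% and 24% with posttest 1 week after each condition's own end.

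**Week 24.** The same 3-month question then reaches back to about week 11 or 12, at or after the end of a program of at most 10 weeks.

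**The case against.** The strongest reply is that this concerns one item whose exact dilution rests on assumptions, and that an undiluted test at week 24 is already planned. Much of that stands.

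- **Order and timing are not fixed.** If module order is randomized, as the information given to families may mean, the three content components are diluted equally and the unequal comparison disappears. The dilution does not: each then averages 7/13 with posttest 12 weeks after start (power about 38%) or 4/13 with posttest after the condition's own end (about 20%).
- **A reader might infer that most of the window precedes the tested components in general.** The article does not support that. A component in the first slot loses only 38% to 46% on the week-12 schedule, and My Coach includes a call for the basic modules, so it begins earlier.
- **A reader might take third-slot figures as the result for Who am I.** On listed order it is third only when both other content components are on, a quarter of its on conditions.
- **A reader might infer that in the mediation model the outcome precedes the mediator.** No section pairs mediator and outcome visits, and the analysis section describes mediation of the primary outcome, assessed at week 24.
- **The appendices on measures and schedule are not shown.** They may add detail, but the article itself states the recall period, the visit and its rank as an objective, and these three do not fit together.

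**Conclusion.** The point holds in limited form. As stated, the week-12 frequency score is largely a total over the program period, and for the three content components its posttest effect is biased towards zero. Under the stated assumptions, power for a true d of 0.28 falls from 80% to between about 16% and 51%, depending on component, posttest definition and window length. Full effect from the first day is a generous assumption; a later onset would dilute further. The figures are illustrative because order and exact timing are not fixed; the direction does not depend on them as long as content components start after the window opens.

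The primary outcome, the risk appraisal ratings, the vignettes, the sample size of 317 and the first component-selection step (main effect on the primary outcome at follow-up) are unaffected.

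**What to change.** In Textbox 1, for the risk-situation frequency score only, name week 24 as the main time point and describe the week-12 value as frequency during the program. Keep week 12 as the main visit for measures without a 3-month recall. If this score serves as an outcome in mediation, pair week-12 mediators with the week-24 frequency and adjust for the baseline of each.

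This changes wording only: the secondary objectives already call for these outcomes at follow-up. The cost is a later result for this one score and probably somewhat more loss to follow-up than at week 12.

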#### Mediators and Moderators

Caregivers and children will complete a battery of web-based questionnaires assessing potential moderators and mediators. Multimedia Appendix 2 provides the full list of measures. *Mediators* comprise a range of measures on relationship-related risk-taking cognitions, detection of risk and safety signals in relationships, emotional security, parental discord in front of the child, attachment, caregiver’s support with identity construction, program adherence, self-appraisal, belongingness, emotional regulation, parental self-care, and child behavior problems. Child’s gender, contact with the biological family, type of maltreatment, executive functioning, and parental childhood trauma will be assessed as *moderators*.

### Statistical Analysis

#### Analyses

Before the analyses, missing data will be examined and appropriately handled using multiple imputation or full information maximum likelihood estimation. To investigate the effectiveness of each intervention component, the primary analyses will test the pre–follow-up change in children’s revictimization composite scores. The primary analysis will be conducted in an intention-to-treat sample. We will use the analysis of covariance with main and interaction effects on the primary and secondary end points. The main effects and interactions are estimated based on aggregates (each reflecting the presence or absence of a specific component) across the 16 experimental conditions. The main effects will be modeled as a fixed effect with baseline levels of an outcome as a covariate and an assumed type I error of *P*<.10 (recommended for component selection [22]). To examine the hypotheses related to mediating and moderating effects, we will use regression analyses. Mediational analyses will be conducted by analyzing the indirect effects of each component on the primary outcome via the assumed mediators (Figure 1). Moderator analyses will be modeled in steps with baseline predictors (eg, type of maltreatment) and then as a second model including interactions with the main effect by condition.

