We will also answer the following four questions to establish how well the conceptual model captures the relevant mechanisms of the intervention (mediation analyses, adapted from the study by Smith et al [56]): how well will the three mediators (relationship-related risk, relationship-related safety, and constructing an identity) predict the occurrence of revictimization, how well does each module content (*Watch Out*!, *You are safe here*, and *Who am I and where do I belong*?) and the coach evoke each of the 3 mediators, how much of the relationship between the intervention’s content components and revictimization is explained by the 3 hypothesized mediators, and how much variability between the content components and revictimization will remain unexplained.

Furthermore, the following variables were identified as potential moderators of intervention (component) efficacy based on the literature review in phase 1:

Child executive functioning (ie, an impaired “ability to shift, inhibit, and focus attention; maintain focus in the face of distracting information” [28]): Reduced executive functioning will lead to smaller intervention effects.Gender of the child [27,57]: We expect worse outcomes in girls than boys.Type of maltreatment [7-9]: Sexual maltreatment experiences will lower the intervention effect compared with other types.Contact with the family of origin [58]: We assume that conflictual contact may reduce intervention effects.Caregiver’s history of child maltreatment [59]: We expect caregivers with such a history to benefit less from the intervention.

Taken together, we use the MOST framework [22] to optimize a web-based program for foster parents, which comprises 4 intervention components. To optimize the program, the primary aim of this study is to examine the efficacy of each component on the primary and secondary outcomes. This paper outlines the protocol (version 01) or the factorial trial, following the SPIRIT (Standard Protocol Items: Recommendations for Interventional Trials) guidelines for clinical trials (Multimedia Appendix 3 provides the SPIRIT checklist).

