### Study Design

The EMPOWERYOU project (funded by the German Ministry of Education and Research, Project code FKZ 01KR1806D) aims to develop and optimize a web-based parenting program by using the MOST framework [22]. This study will use a 2×2×2×2 full factorial design by randomly allocating participants to 1 of 16 experimental conditions (Table 1). To estimate the main effects of the 4 intervention components and their interactions, data from all the experimental conditions will be used. For example, the effect of the component *Relationship-related risk* will be estimated by comparing the mean of the experimental conditions 1 to 8 with the mean of the conditions 9 to 16 (Table 1). Families in the first condition will not receive any experimental component but will be delivered the 2 basic intervention modules that every caregiver receives. Families will be informed that everyone may access all modules and that the sequence and timing of each module will be based on a randomization procedure.

**Table 1 table1:** Experimental intervention conditions (optimization schema).

Experimental condition	Component 1: *Watch Out*!—relationship-related risk	Component 2: *You are safe here*—relationship-related safety	Component 3: *Who am I and where do I belong?*—identity	Component 4: *My Coach*—professional support
1	Off^a^	Off	Off	Off
2	Off	Off	Off	On^b^
3	Off	Off	On	Off
4	Off	Off	On	On
5	Off	On	Off	Off
6	Off	On	Off	On
7	Off	On	On	Off
8	Off	On	On	On
9	On	Off	Off	Off
10	On	Off	Off	On
11	On	Off	On	Off
12	On	Off	On	On
13	On	On	Off	Off
14	On	On	Off	On
15	On	On	On	Off
16	On	On	On	On

^a^Not included in the intervention.

^b^Included in the intervention.

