### Sample Size Calculations

Anticipated effect sizes were estimated from the reported effect sizes for victimization and revictimization interventions, which also included (1) facilitating risk detection skills; (2) social skills, such as problem-solving or conflict management; (3) skills to build healthy relationships; and (4) the ability to reflect on own expectations that relationships will include harm [28,60,61]. We expect small to moderate effect sizes between Cohen *d*=0.28 and Cohen *d*=0.46 for the main effects of specific intervention components (component 3: 0.46, component 4: 0.28, and component 6: 0.32). Thus, a sample size of 317 was determined as necessary to detect the smallest anticipated effect size of Cohen *d*=0.28. To detect this difference with the analysis of covariance as the suggested method for component selection by the developer of the factorial design (groups=2, *df*=1, covariate=1) with 80% power at α=.10 per intervention component or interaction, a sample size of 317 is required (calculated with FactorialPowerPlan SAS Macro provided by [name] [62]). We will use an intention-to-treat approach, although only one family dropped out during the intervention period in the pilot study. In contrast, findings from the pilot study showed that 26% (4/15) of the recruited caregivers that registered for the website dropped out before the intervention. Therefore, we consider a dropout rate (before the allocation to condition) of 26%. Therefore, we aim to recruit a total of 429 families. Recruitment will be stopped as soon as we reach the sample size needed for the analysis (N=317).

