#### Randomization and Blinding

Families will be randomized to 1 of the 16 experimental conditions via a database that uses concealed, computer-generated [63], permuted block randomization, with stratification by child’s gender and with fixed block sizes of 16 (conditions were randomized within each block). Randomization procedures will be completed by another research group within the EMPOWERYOU consortium that is not associated with the intervention trial otherwise (Neuropsychology at the University Hospital Aachen, Germany) to minimize the occurrence of potential biases (eg, biases that may arise through primary caregivers’ or researchers’ preferences). Study staff at the University of Bremen will not view the allocation sequence to minimize researchers’ prediction biases. The database will not reveal participants’ treatment conditions to the study staff until after the family’s eligibility is verified (after preintervention assessment). Families will be informed of their allocation status after baseline data collection is completed to ensure that participants are blind to allocation during the initial assessment. In the case of instances of harm or severe abuse to a child being reported by a participant, the allocation status of the participant will be unblinded. All cases of unblinding will be reported to the Data Safety and Monitoring Board (DSMB).

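### The primary ANCOVA as stated omits child's gender, the only randomisation stratum; if gender predicts outcome beyond baseline, the component tests are slightly conservative (minor)

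*Protocol article*

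**What the plan says.** The Randomization and Blinding section describes permuted blocks "with stratification by child’s gender and with fixed block sizes of 16". Gender is the only stratification factor.

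The Analyses section plans an analysis of covariance with main and interaction effects of the four components. On adjustment it says: "The main effects will be modeled as a fixed effect with baseline levels of an outcome as a covariate", with "an assumed type I error of *P*<.10". Gender is not mentioned there.

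The Sample Size Calculations section uses the same structure: "covariate=1) with 80% power at α=.10 per intervention component or interaction".

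Gender does appear in the list of potential moderators under Objectives and Hypotheses, with the remark "We expect worse outcomes in girls than boys", and again under Mediators and Moderators. Moderator analyses are separate stepwise regression models, not the primary ANCOVA.

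**The concern.** Stratified blocking balances girls and boys across the 16 conditions, so a gender difference in outcome contributes almost nothing to the true sampling variance of a component contrast. A model without gender does not know this and counts the between-gender variance as residual error. Where gender matters for outcome, the reported standard errors then exceed the real ones, and a test labelled P<.10 runs below 10%.

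This has some relevance here because the Decision-making Process section selects components by significance, the 10% level was chosen for that purpose, and the sample size gives 80% power with nothing to spare for the smallest anticipated effect. In addition, 317 is not a multiple of 16 (19 × 16 = 304, remainder 13), so at least one gender stratum must end in an incomplete block. A gender term would also absorb that small imbalance.

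**Working it through.** **Inputs from the article.** N = 317 ("a sample size of 317 is required"); d = 0.28 ("necessary to detect the smallest anticipated effect size of Cohen *d*=0.28"); α = .10; power 80%; one covariate; each component split 1:1, for example "comparing the mean of the experimental conditions 1 to 8 with the mean of the conditions 9 to 16".

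**Assumed, because the article gives no figure.** R² is the share of the baseline-adjusted residual variance explained by gender, taken as 0 to 5%. With half the children girls, a gender gap of g within-gender residual SDs corresponds to R²/(1 − R²) = g²/4. So R² = 1% means g ≈ 0.20, and R² = 5% means g ≈ 0.46.

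**1. Reproduce the plan's figure.** For a two-sided test at α = .10, the normal approximation gives 158 per level, 316 in total. The noncentral t gives 317 with power 0.800. (One-sided α = .10 would give 230, and two-sided .05 would give 402.) The stated 317 is reproduced. Spending up to 17 degrees of freedom on the model leaves 317 unchanged.

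**2. Standard error.** Model SE without gender divided by model SE with gender = 1/√(1 − R²):
- R² = 0: 1.000
- R² = 1%: 1.005
- R² = 5%: 1.026

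**3. True type I error without gender.** Because the design has balanced gender, the estimate varies with the smaller SE but is judged against the larger one. True α = 2[1 − Φ(1.645/√(1 − R²))]:
- R² = 0: .100
- R² = 1%: .098
- R² = 5%: .091

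**4. Power, with d in within-gender SDs.** The expected test statistic is 0.28 × √317 / 2 = 2.493.
- With gender in the model: Φ(2.493 − 1.645) = .802.
- Without gender: Φ(2.493 − 1.645/√(1 − R²)) = .799 at R² = 1% and .790 at R² = 5%.
- Loss: 0.2 to 1.2 percentage points.

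**5. Power, with d in SDs that include the gender variance.** The noncentrality with adjustment is 317 × 0.0196/(1 − R²). Power is then 80.4% at R² = 1% and 81.8% at R² = 5%, against the nominal 80.0%. The gain of 0.4 to 1.8 points is an upper figure, because the unadjusted test in a stratified design already does a little better than nominal: Φ(0.848/√0.95) = .808 at R² = 5%.

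**6. Simulation check.** The 2⁴ trial was simulated with N = 317, blocks of 16 within gender, all interactions and a baseline covariate, 4,000 runs per setting:

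| g | Type I error, without / with gender | Power at d = 0.28, without / with gender |
|---|---|---|
| 0 | .102 / .102 | .794 / .794 |
| 0.5 | .093 / .103 | .778 / .790 |
| 0.8 | .079 / .102 | .754 / .799 |

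The Monte Carlo standard error is about .005 for type I error (√(.1 × .9/4000)) and about .006 for power (√(.8 × .2/4000)). The simulation agrees with the formulas in direction and approximate size. The row g = 0.8 lies well outside the assumed range and is shown only as an extreme.

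**The case against.** Four arguments can be made against the point.

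**The effect is conditional, and the evidence for the condition is thin.** Everything depends on gender adding to the baseline score as a predictor. A stable difference between girls and boys would already be carried largely by the baseline. The remark about worse outcomes in girls stands in a list of moderators of component efficacy, whose other entries concern smaller treatment effects. It can be read as a prognostic statement or as a weaker response to the intervention. This objection stands. A reader might infer that the article declares gender prognostic and that the standard errors are therefore too large as a matter of fact; the text supports neither.

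**The size is small.** An R² of 5% needs a gender gap of about 0.46 SD after baseline adjustment, as large as the largest component effect the article anticipates (d = 0.46). At half that gap the loss is a fraction of a power point. This also stands and sets the severity.

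**The full protocol or SAP may include gender.** It may, and the Analyses section does not say that the baseline score is the only covariate. But the article is not silent: it names its covariate, and its power calculation counts one. As described, the primary model does not reflect the randomisation. For the imputation or full-information likelihood model the objection is stronger, since the article leaves even the choice of method open; that part of the fix follows from the main change and is not a separate fault.

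**Gender is used in the moderator models.** It is, but those are separate from the primary analysis and do not change its standard errors.

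**Conclusion.** The stated primary analysis does not carry the stratification factor of the randomisation. This is a minor matter of efficiency and consistency. If gender explains 1% to 5% of the baseline-adjusted residual variance, an assumption that no figure in the article supports or refutes, standard errors are overstated by about 0.5% to 3% and true α lies between about .098 and .091. The power cost is at most about 2 points, and 0.2 to 1.2 points once the balance already achieved by the design is counted. If gender explains nothing beyond baseline, there is no cost.

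A reader might also infer that the omission biases the component effects or makes the tests invalid. It does neither: allocation is randomised and balanced on gender, so the estimates are not biased, and the error rate moves below the nominal level, not above it. Nor is it shown that any component-selection decision would change materially.

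**What to change.** State child's gender, the randomisation stratum, as a fixed covariate in the primary and secondary ANCOVAs alongside the baseline level of the outcome, and include it in the imputation or full-information maximum likelihood model. If the full protocol or SAP already does this, bring the article's description into line.

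The cost is one degree of freedom out of about 300. N = 317 is unchanged, and gender is already known at randomisation, so nothing new is collected. The change can be made without knowledge of results: recruitment was still under way at the time of the article (181 families by October 2022), and the Decision-making Process section keeps assignment blinded in the data set until component selection is complete.
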